#### 3.6.3 Interim analysis.

An interim analysis will be conducted at the halfway (when we reach half the numbers) point of recruitment to assess the safety and the primary outcome endpoints. An independent statistician will perform the analyses, and the data safety monitoring committee will determine the results and decide about the trial’s continuation as designed.

#### 3.6.4 Cost-effectiveness analysis.

Medical costs will be calculated using a micro-costing approach with overhead costs allocated using the step-down method. Unit costs will be supplied from the hospital finance department or derived using provincial health ministry records. Healthcare resource utilization will be defined as the number of clinic visits for surgical, family medicine, and other visits. To capture episodes that do not occur within our healthcare network, a validated healthcare resource utilization questionnaire will be administered to patients at 45-days. The primary effectiveness measure of the economic evaluation will be utilities, which will be mapped and derived from the SF-36.

### 3.7 Risks benefits and exclusion of participants

Prehabilitation has been shown to be useful at reducing postoperative complications in high-risk patients. We expect that patients in the prehabilitation group will benefit from the intervention as it is intended to be a multimodal optimization tool prior to surgery. We expect them to improve their preoperative aerobic and functional capacity status, strength, nutritional status and to recover faster postoperatively with less postoperative complications. Based on previous literature of exercise in patients with AAA, we do not expect the presence of serious adverse exercise-related events. For instance, Weston et al. reported no serious adverse events in their HIIT trial in AAA patients, and only an event rate of 1.8 per 100 person-hours. (CI 0.4–9.6 events) for non-serious adverse events [81]. Nevertheless, a series of measures will be put in place to make sure that safety prevails throughout the study. Firstly, participants will be excluded if they present any contraindication to exercise. Furthermore, patients will undergo a cardiopulmonary exercise testing that will act both as a screening tool to uncover any non-diagnosed cardio-respiratory pathology and as safety tool by allowing us to determine the safe limits of exercise training. A referral to a specialist (cardiologist, pneumologist, internist) will be made if any event occurs during the assessments or training and the participant will be excluded from study participation.

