## 3. Methods and analysis

### 3.1 Trial design and ethics

The trial protocol was written following the Standard Protocol Items: Recommendations for Interventional Trials (SPIRIT) guidelines [54]. This is a prospective, international, multicenter, open label, randomized controlled trial with an allocation ratio 1:1 comparing standard of care versus 6 weeks of a multimodal prehabilitation program. The recruitment period started in September 2024 and will last until September 2027. Recruitment of participants will take approximately three years, the follow-up and data collection after recruitment phase will last one year, and results will be analysed within a year of finishing. Both primary endpoint and baseline data will be blindly assessed. Intention-to-treat criteria will be used to define the analysis population; all randomized participants will be included in the analysis according to assigned group. The trial is registered on the Registry of National Institutes of Health ClinicalTrials.gov, a database of privately and publicly funded clinical studies conducted around the world (NCT05756283). The trial will be conducted according to the rules of Good Clinical Practice. The study will be conducted according to the principles of the Declaration of Helsinki and in accordance with the Medical Research Involving Human Subjects Act (WMO) and has been reviewed by the ethics board of McGill University Health Centre MP-37-2023-8983. No datasets were generated or analysed during the current study. All relevant data from this study will be made available upon study completion.

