### 3.4 Study outcomes

#### 3.4.1 Primary outcome.

The primary outcome of this study is the incidence of postoperative complications measured by the Comprehensive Complication Index. The CCI was developed to address some of the limitations of traditional surgical morbidity reporting, such as only reporting the most severe complication or only picking the most common types of complications [55,56]. It provides a continuous score from 0 (no complications) to 100 (death) that integrates the cumulative burden of all complications and their severity. It has been validated in surgical abdominal, urologic, and cardiothoracic patient populations [47,57,58]. It correlates better than any other scale with respect to length of stay, cost/burden to the health care system, readmissions, and disability [59–61].

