#### 3.5.1 Participant screening, recruitment and informed consent (T-1).

In all participating centers, participant selection will begin after a high probability of having open AAA repair is stablished by the perioperative vascular team. Within one week of the decision to go for surgery, a medical research team will screen for health conditions that preclude study participation. The participant will be contacted by a study coordinator who will ask for willingness to participate in the study. The participant will be offered the possibility to participate in the trial and, if the participant agrees, a first baseline appointment (T0) will be scheduled where written and oral information about the trial will be given.

The study coordinator will answer any questions that participants might have and ask if the patient is willing to participate in the trial. The right of a patient to refuse participation without giving reasons will be respected. The patient will remain free to withdraw at any time from the study without consequences for further treatment.

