***Randomization*:** Randomization will be performed after baseline assessment. Participants will be randomized to both arms equally a (1:1 ratio) upon final confirmation of eligibility. A stratified randomization will be performed by site and sex; with block size 2,4 and 6 to ensure unbiased allocation of the patients. Allocation to study group will be revealed using RedCap software to the research team that will carry out the intervention once baseline assessment is completed.

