#### 3.5.4 Multimodal Prehabilitation program (MP) (T1-T6).

Participants in the intervention group will undergo, in addition to the standard of care, 6 ± 1 weeks of a personalized multimodal prehabilitation program. The interventions included will be patient-centered, aiming to optimize patients’ preoperative health status while enhancing their empowerment and engagement. The main components of the program will consist in:

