#### 3.6.2 Primary analysis.

The primary analysis will be conducted by the intent-to-treat approach; differences in CCI scores between MP and the standard-of-care arms will be assessed in 45 days. Descriptive statistics will be performed using means, proportions, medians, standard deviations, and interquartile ranges, as appropriate depending on the nature of the data. We will use Generalized Linear Mixed or Generalized Estimation Equation models to evaluate the impact of the intervention, accounting for between and within group differences. The effect of MP on specific postoperative complications will be analyzed using parametric tests for categorical variables. The effect of MP on functional improvement and quality of life will be analyzed using time interactions with the group after considering the site at a random level. In addition, we will perform the sensitivity analysis based on a per-protocol approach using mixed effects, with study site as the random effect to cross-validate our results. We also plan to perform subgroup analyses of the primary outcome measure, as well as MP adherence on the following groups: study site, sex, and other variables which have previously been shown to impact MP adherence as well as postoperative outcomes after AAA repair, such as age, diabetes, renal failure, and baseline functional status.

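### Section 3.7 excludes participants from the study after any event in training or assessments, which falls mainly on the prehabilitation arm and conflicts with the all-randomised analysis

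*Protocol article*

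**What the plan says.** Section 3.7 describes the safety measures and ends with a consequence for the participant: a referral to a specialist "will be made if any event occurs during the assessments or training and the participant will be excluded from study participation". No grade or type of event is specified there, and nothing says that complications or later outcomes are still collected. The same section expects no serious exercise-related events and cites, for non-serious events in an earlier trial of interval training in AAA patients, "only an event rate of 1.8 per 100 person-hours", with an interval of 0.4 to 9.6.

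On the analysis, section 3.1 states that "all randomized participants will be included in the analysis according to assigned group", and section 3.6.2 repeats it: "The primary analysis will be conducted by the intent-to-treat approach".

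On timing and exposure, section 3.5.2 says "Randomization will be performed after baseline assessment". Section 3.5.4 gives the programme to one arm only: "Participants in the intervention group will undergo, in addition to the standard of care, 6 ± 1 weeks of a personalized multimodal prehabilitation program". Both arms repeat exercise testing before surgery (T7, section 3.5.5) and the 6-minute walk test six weeks after discharge (T9, section 3.5.7).

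**The concern.** A rule that takes people out of the study after randomisation is harmless to the comparison only if it is unrelated to arm and to prognosis. This one is tied to arm, because only one arm trains. It may well be tied to prognosis, because a participant who has an event under exercise load is plausibly a worse operative risk.

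If sites apply the sentence literally, they stop study procedures for that person and the CCI is never entered in the case report form. The intention-to-treat statement then has no data to work on for those participants. A statistical analysis plan could choose a missing-data method, but it could not recover outcomes that were never recorded. The likely direction is a prehabilitation arm that looks healthier than the one that was randomised.

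**Working it through.** **Step 1. When and in whom the rule can act.**

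| Contact | Relative to randomisation | Arms exposed |
|---|---|---|
| Baseline tests (T0, section 3.5.2) | before | not yet allocated |
| Training (T1–T6, section 3.5.4) | after | prehabilitation only |
| Preoperative tests (T7, section 3.5.5) | after | both |
| Postoperative walk test (T9, section 3.5.7) | after | both |

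Exclusions at the baseline cardiopulmonary exercise test come before randomisation and do not conflict with intention to treat. The conflict is confined to the last three rows, and only training is one-sided. The loss is therefore mainly, not solely, in the prehabilitation arm.

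**Step 2. Arm size (section 3.6.1).** The plan gives 126 evaluable and 152 randomised, 76 per group. Per arm, n = 2 × (1.96 + 0.84)² × SD² / difference². With SD 20, a difference of 10 gives 63 per arm, or 126 in total. The written difference of 30 gives 7 per arm, or 14 in total. So 126 matches a difference of 10, which the article does not state. That is a separate matter. Here I use only the 76 per group, which is 63 × 1.2 = 75.6, rounded up. The allowance for loss is therefore 76 − 63 = 13 per group.

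**Step 3. How many could leave because of training.** Inputs: two supervised hours a week (section 3.5.4) for 6 weeks, so 12 hours each, and the rate cited in section 3.7. Assumptions: the rate carries over to this trial, events follow a Poisson process with a constant rate, only supervised hours count, and every event leads to exclusion.

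- Person-hours: 76 × 12 = 912.
- Expected events: 912 × 1.8 / 100 = 16.4.
- Share with at least one event: 1 − exp(−0.018 × 12) = 1 − exp(−0.216) = 0.194.
- Participants: 0.194 × 76 = 14.8, about 15, leaving 61.

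| Rate per 100 h | Share with ≥1 event | Prehabilitation, of 76 | Control, because of training |
|---|---|---|---|
| 0.4 | 0.047 | 3.6 | 0 |
| 1.8 | 0.194 | 14.8 | 0 |
| 9.6 | 0.684 | 52.0 | 0 |

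At 1.8 per 100 hours, a programme of 5 or 7 weeks (10 or 14 hours) gives 12.5 or 16.9 participants. If only about 45 minutes of each session counts as interval training, exposure is 9 hours: 1 − exp(−0.162) = 0.150, about 11 participants.

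**Step 4. Possible shift in the mean CCI.** Let p be the share removed and D the amount by which their mean CCI would exceed that of those who remain. The full-arm mean is the remaining mean plus p × D, so removal lowers the observed mean by p × D. The documents give no value for D. With p = 0.194:

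- D = 5: 0.97, about 1.0 point.
- D = 10: 1.94, about 1.9 points.
- D = 20: 3.88, about 3.9 points.

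With D = 10 and the two ends of the rate interval, the shift is 0.5 and 6.8 points. If D is zero there is no bias from this source, only lost precision.

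**The case against.** The best defence is that section 3.7 is a safety section and does not define the analysis set. Study participation could have been meant as training and testing, and on that reading it is compatible with sections 3.1 and 3.6.2. This stands to the extent that the article does not show an intention to drop these people from the CCI analysis, and a reader who infers such a plan goes further than the text. But the benign meaning is not what is written. Section 3.5.2 uses almost the same expression for true removal after the baseline exercise test, and section 3.5.4 handles poor tolerance of exercise by adjusting the session, without anyone leaving the study. Nothing says that follow-up continues.

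A second defence is that the event is linked to specialist referral, which suggests something clinically significant, and that the adverse-event list (S5 File) is not shown. This also stands. The 15 of 76 is what the literal wording would produce at a non-serious event rate, not a forecast.

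Three stronger inferences are tempting, and the documents do not support them:

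- A specific inflation of the false-positive rate. It would need a known CCI excess in those removed, which is not given, and a design difference that is only inferred from the sample size.
- That harm before surgery is concealed. Section 3.4.2 records adverse events during assessments and intervention as the safety outcome, section 5 sends severe events to the safety board within 24 hours, and section 5.1 names rupture among the serious events.
- That the plan is defective for not scoring participants who die waiting or never have open repair. That choice is commonly left to the statistical analysis plan, which is not shown.

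**Conclusion.** The point holds as a conflict in wording with a real consequence. Followed as written, section 3.7 creates post-randomisation loss mainly in one arm, plausibly related to prognosis, and it cannot be squared with analysing everyone randomised. This conclusion needs no arithmetic.

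The size is uncertain. Under the literal reading and the cited rate, about 15 of 76 would leave the prehabilitation arm, slightly more than the 13 per group allowed for all losses. The interval runs from 4 to 52, and the number is lower if only significant events trigger the rule. The resulting shift in mean CCI is about 1.0 to 3.9 points for an assumed excess of 5 to 20 points, against a planning SD of 20. Both the excess and its direction are assumptions.

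**What to change.** Reconcile section 3.7 with sections 3.1 and 3.6.2. Replace exclusion from the study with wording that separates two things: stopping training or testing, which is a clinical decision on which no rule is proposed here, and leaving the study. State that a participant with an event after randomisation stays in follow-up, has the CCI recorded at the surgical admission and other outcomes at the later visits, and is analysed in the assigned arm. Keep the exclusion at the baseline exercise test as it is, since it precedes randomisation.

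The cost is a protocol amendment and an instruction to sites. The CCI comes from the daily blinded assessment during admission (section 3.5.6), so that assessment and the later contacts must go ahead for these participants too. Recruitment began in September 2024, so sites should also check whether anyone has already been excluded under this rule and, where consent allows, resume follow-up.

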## 4. Data collection, handling, and monitoring

De-identified data will be collected in different timepoints (Fig 1). The de-identified data will be uploaded in an electronic CRF using Research Electronic Data Capture (REDCap). The REDCap server containing de-identified data will be located in the McGill University Health Centre Research Institute facility.

### 4.1 Data Monitoring Committee

A Data Monitoring Committee (DMC) will be established to ensure data quality and transparency. This committee will be responsible of training research staff on data management and electronic CRF. The committee will also be responsible of ensuring that all sites have all the necessary requirements, material an equipment to initiate the trial and will monitor study procedures, as well as adherence to the protocol throughout the study. Should any protocol deviation occur during the trial in any of the sites, it will be documented and reported to the data monitoring committee.

## 5. Data Safety Monitoring Board (DSMB)

A Data and Safety Monitoring Board (DSMB) will be created for this trial. It will be formed by an independent group of experts. Their responsibilities will be to review the protocol before the trial starts, review and assess the study data for participant safety, evaluate study conduct, milestones, progress, and efficacy. They will be responsible of making recommendations concerning the continuation, modification, or termination of the trial.

The different research personnel of all trial sites will be responsible of reporting to the principal investigator any exercise-related adverse events during the assessments or the MP period. The PI will immediately report severe adverse events to the Data Safety Monitoring Board and the sponsor (within 24h of the SAE incidence).

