#### 3.4.2 Secondary outcomes.

Secondary outcome measures will fall into 5 categories:

Healthcare-related: Intraoperative complications, ICU length of stay, hospital length of stay, reintervention, 6-week and 1-year mortality/ readmission/ emergency room visit and prehabilitation cost-effectiveness.Change in functional and aerobic capacity measured by:6-minute walk test: the 6MWT evaluates the ability of an individual to maintain a moderate level of physical activity reflective of the activities of daily living [62]. As daily activity is mostly pursued at a submaximal level, functional walking capacity is a more direct measure of capacity for daily routine. Therefore, it is a useful tool to assess postoperative recovery and return to normal life [63].VO2-peak, VO2-AT, VE/VCO2-AT: Cardiopulmonary Exercise Testing (CPET) is the current gold standard to assess aerobic capacity [64]. It provides an assessment of the integrative exercise responses involving the pulmonary, cardiovascular, hematopoietic, and skeletal muscle systems [64]. VO2 peak, VO2-AT and VE/VCO2-AT are CPET derived variables that predict postoperative morbidity and mortality, as well as indicators of cardiorespiratory fitness.Yale physical activity survey (YPAS): YPAS is a self-reported measure of physical activity, comprising 18 activities evaluated according to the total number of hours done during an average week [65].Patient reported outcomes:Health-related quality of life (SF-36): the SF-36 is the most widely used health-related quality of life measure and has been validated for surgical populations. It incorporates behavioral functioning, subjective wellbeing, and perceptions of health. Two summary scores have been developed: the Physical Component Summary and the Mental Component Summary, standardized to have a mean of 50 and a standard deviation of 10. A higher score on the SF-36 sub-scales or component summary measures indicates a better quality of life. A change of as little as 2 units on the physical component summary has been shown to be the minimum clinically meaningful change; 5 points is often targeted by medical intervention studies, though surgical interventions can have an impact as large as 10 points [66,67]. Data obtained from the SF-36 will be used to calculate the quality adjusted life years using the SF-6D [66].Hospital Anxiety and Depression Scale (HADS): HADS is a reliable instrument for screening clinically significant anxiety and depressive symptoms in medically ill patients [68]. It has also been shown to be a valid measure of their severity [68]. It includes items that assess generalized depression and anxiety, including tension, worry, fear, panic, difficulties in relaxing, and restlessness.Nutritional status outcomesPatient Generated Subjective Global Assessment (PGSGA): the PGSGA is a screening tool used to identify malnutrition and consists of two parts. The first part is the Patient Generated Subjective Global Assessment Short Form which is a widely validated malnutrition screening tool and has been previously used in vascular surgery [69–71]. The second part is completed by a dietitian and includes a physical examination, where fat and muscle stores and fluid status are evaluated, and an assessment of the disease/condition. The global score generates a subjective category rating for nutritional status.Body composition: Weight, BMI, Fat free mass (kg) and body fat mass (%) will be assessed using bioimpedance.Diet: A registered dietitian will assess usual energy and protein intake, including supplements, at baseline and pre-surgery using three-day food records or 24-hour dietary recalls.Study related outcomes:Compliance: compliance to supervised and home-based exercise will be calculated by counting the number of sessions attended by the participant. Home-based exercise compliance will be estimated by counting the number of sessions they logged in an exercise logbook. Compliance to nutrition will be evaluated based on the assessment of dietary changes/goals set by the dietitian. Every week participants will be asked if the nutrition goals set have been met.Fidelity: fidelity to supervised and home-based exercise will be recorded. Supervised exercise fidelity will be measured by recording the watts (for endurance training) and kg (for strength training) at which the participants train during the session (versus expected according to the individualized plan) as well as heart rate and RPE for both breathing and muscular fatigue [72].Satisfaction and acceptability of the intervention: a satisfaction survey enquiring about the different components of the prehabilitation will be given upon completion of the intervention (S1 File).Safety: safety will be assessed by recording the appearance of any adverse event occurring during assessments or intervention. A list of adverse events can be found in S5 File.

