#### 3.5.5 Preoperative assessment (T7).

Six weeks after the baseline assessment, or the week prior to surgery if surgery happens >6 weeks after baseline, participants will undergo a preoperative assessment with the same measurements performed at baseline assessment (resting blood pressure, heart rate oxygen saturation, body composition, PG-SGA, 6-Minute Walk Test, CPET, YPAS, SF-36, HADS questionnaire). Participants will be offered the possibility to continue training until their week of surgery; in case it gets delayed. In addition to these measurements, the intervention group will be invited to fill out a satisfaction survey regarding the different components of the prehabilitation group that can be found in the S1 File.

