### 5.1 Premature termination of the study

The DSMB will decide to terminate the trial in case of significantly increased incidence of serious adverse events. Serious adverse events might include aneurysm rupture, cardiac arrhythmias, or other potential exercise-related events during CPET or exercise sessions (S5 File for full list of adverse events).

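### Before surgery, adverse event recording is tied to assessments and the intervention, so safety counts are not comparable between arms, and the DSMB termination rule names no comparator

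*Protocol article*

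**What the plan says.** Four parts of the protocol article bear on this.

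- **Safety outcome (3.4.2):** "safety will be assessed by recording the appearance of any adverse event occurring during assessments or intervention".
- **Reporting duty (5):** site staff are responsible for "reporting to the principal investigator any exercise-related adverse events during the assessments or the MP period". The next sentence says "The PI will immediately report severe adverse events to the Data Safety Monitoring Board and the sponsor", within 24 hours. That sentence is not limited by arm or by cause.
- **Termination (5.1):** "The DSMB will decide to terminate the trial in case of significantly increased incidence of serious adverse events". The examples are aneurysm rupture, arrhythmias and "other potential exercise-related events during CPET or exercise sessions". No comparator, time window or threshold is given.
- **Interim analysis (3.6.3):** safety is assessed alongside the primary outcome at the halfway point of recruitment.

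On the timing of contacts, section 3.5.2 states "Randomization will be performed after baseline assessment", so T0 is not a post-randomisation observation. Section 3.5.3 gives controls each site's standard care during T1-T6 and describes no trial contact. At T7 (3.5.5), in both arms, "participants will undergo a preoperative assessment with the same measurements performed at baseline assessment". The intervention arm has "6 ± 1 weeks of a personalized multimodal prehabilitation program" (3.5.4), with two supervised sessions a week, at least two dietitian sessions and at least one psychological session.

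**The concern.** Both recording rules are defined by the intervention. The rule in section 5 also filters on presumed cause. A control can have an exercise-related event in a trial setting only at T7. A serious event in a control at home in week 3 is outside both rules as written. A serious event in a prehabilitation participant that is judged unrelated to exercise is outside the site reporting duty.

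Aneurysm rupture heads the list of serious events in section 5.1. It can occur in either arm, with or without exercise. Randomisation offers an unbiased comparison of pre-surgical serious events between patients who train with an unrepaired aneurysm and patients who do not. That comparison needs the same events to be looked for in the same way in both arms. If they are not, a difference in counts mixes risk with observation, and the DSMB cannot separate the two.

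The problem is confined to the period between randomisation and surgery. Complications during admission are assessed daily under blinding in both arms (3.5.6), so the primary outcome is not affected by it.

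**Working it through.** **1. Scheduled contacts after randomisation and before surgery**

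| Contact (section) | Prehabilitation | Control |
|---|---|---|
| Supervised sessions, 2 per week x 6 weeks (3.5.4) | 12 | 0 |
| Dietitian (3.5.4) | at least 2 | 0 |
| Psychological session (3.5.4) | at least 1 | 0 |
| T7 (3.5.5) | 1 | 1 |
| Total | at least 16 | 1 |

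Over the permitted 5 to 7 weeks, the prehabilitation minimum runs from 10 + 2 + 1 + 1 = 14 to 14 + 2 + 1 + 1 = 18. Counting only supervised sessions and T7 gives 12 + 1 = 13 against 1.

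**2. Does T7 look back?** The measurements listed for T7 include no enquiry about events since baseline. By contrast, the six-week postoperative visit (3.5.7) collects emergency visits and readmissions since discharge, and the one-year follow-up (3.5.8) adds a review of hospital records. The article thus describes retrospective collection after discharge in both arms, but not between randomisation and surgery.

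**3. Would a plausible imbalance count as significant?** The article gives no event risk, detection rate or test for section 5.1, so there is no figure to reproduce. Assume a 5% risk in each arm: 0.05 x 76 = 3.8, or about 4 events. In the extreme case of 4 seen under prehabilitation and 0 in controls, the two-sided Fisher p is

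2 x C(76,4)/C(152,4) = 2 x (76 x 75 x 74 x 73)/(152 x 151 x 150 x 149) = 2 x 0.0600 = 0.12.

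This is not significant at 5%. Five against 0 gives 0.1200 x 72/148 = 0.058. Six against 0 gives 0.0584 x 71/147 = 0.028.

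**4. Sensitivity.** Assume equal true risk, full detection under prehabilitation, a fraction d detected in controls, and a two-sided Fisher test at 0.05. Summing exact binomial probabilities gives the chance of a false significant excess under prehabilitation:

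| Per arm | True risk | d = 1 | d = 0.5 | d = 0.25 | d = 0.1 |
|---|---|---|---|---|---|
| 40 (interim) | 5% | 0.2% | 0.5% | 0.9% | 1.1% |
| 40 | 10% | 0.8% | 4.2% | 9.4% | 15.0% |
| 40 | 20% | 1.4% | 16.2% | 41.1% | 64.4% |
| 76 (final) | 5% | 0.8% | 3.8% | 8.3% | 13.2% |
| 76 | 10% | 1.4% | 13.1% | 34.4% | 57.7% |
| 76 | 20% | 1.5% | 32.8% | 76.7% | 95.7% |

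Every risk and every d is an assumption. With equal detection (d = 1) the figure never exceeds 1.5%. With d below 1, the expected ratio of observed counts is 1/d although the true ratio is 1.

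**The case against.** **The termination rule names no comparator.** This is right. A between-arm comparison is one reading; a pooled or external benchmark is equally possible. But an incomplete count of control events would also distort a pooled rate, and the only external event rate in the article (3.7) concerns non-serious events. The missing comparator is therefore part of the problem.

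**The reporting rule is wider than training sessions.** Section 5 covers the whole intervention period, so home exercise is included, with weekly logbook review (3.5.4). The period could even be read as T1-T6 in calendar time for both arms. The exercise filter would still exclude most control events. The 24-hour sentence is unrestricted, but the only stated route by which sites inform the principal investigator is the restricted one before it.

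**Major events would come to light anyway.** This largely stands. A control who dies, ruptures or has urgent repair would probably be noticed when T7 or the planned operation is missed. A reader might infer that such events would go uncounted in both arms, but the article does not show that. What it lacks is a requirement to report them as safety events.

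**A safe trial could be stopped.** A reader might infer this too. The article does not support it: 4 against 0 is not significant, the high values in the sensitivity table need high risk together with poor detection, and an independent board with the wide remit in section 5 is not bound to a mechanical test.

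**Material not shown may settle the matter.** The legends of Figs 1 and 3 list AE and SAE, and the S5 File holds the event list. They may schedule collection in both arms. If so, sections 3.4.2 and 5 are narrower than the figures and still need to be aligned with them.

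**The trial is too small to compare rare events such as rupture.** This is true, and it limits what equal recording can deliver. It does not justify recording the arms differently.

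**Conclusion.** The point holds as a defect of ascertainment. Sections 3.4.2 and 5 state a rule, followed literally, under which pre-surgical safety counts are not comparable: at least 16 scheduled contacts against 1, with a filter on cause. Any comparison by arm, whether under section 5.1 or at the interim analysis, would be biased towards an apparent excess under prehabilitation. Section 5.1 should also say what an increase is measured against.

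The size of the bias cannot be fixed from the article. At an assumed 5% risk, a false significant excess stays at or below about 13% with 76 per arm, even if only one control event in ten is seen. At higher assumed risks it grows quickly. Under-recording is most plausible for transient or less severe events and least plausible for death or rupture. The conclusion rests on the text shown; Figs 1 and 3 and the S5 File could narrow it to an inconsistency of wording.

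**What to change.** Amend sections 3.4.2, 5 and 5.1 together:

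1. Record all serious adverse events in both arms from randomisation to surgery, wherever they occur and whatever the presumed cause. Include rupture, urgent repair, death, unplanned admission and arrhythmia.
2. Use one method in both arms: the same questions at T7 or on admission for surgery, plus a review of hospital records. This also covers participants who never reach T7 or surgery.
3. Give the DSMB these counts by arm.
4. State in section 5.1 the comparator against which an increase is judged.
5. Keep events during supervised or home training as a separate descriptive list for the prehabilitation arm.
6. Make the AE/SAE entries in Figs 1 and 3 and the S5 File agree with the revised text.

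The cost is about one CRF page and a few minutes per participant at existing contacts, with somewhat more events to report. Recruitment runs to September 2027 (3.1), so the change can still take effect. For participants already past surgery, record review can supply part of the missing information.
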